### **9.2 Randomization and Stratification**

Subjects will not require randomization as this pilot study is a single arm, open label trial. Stratification will occur by gender.

### **9.3 Primary Endpoint Assessments**

VAT volume (cm^2) will be calculated from a single 5 mm slice CT scan obtained at the level of the L4-L5 inter-vertebral disc space. CT scans will be obtained prior to telmisartan initiation and at study termination (Weeks 0 and 24). All CT scans will be standardized and communicated via electronic medium (CD, DVD, or optic disk) to the central reading center at Tufts University. The central reader will be blinded to patient characteristics.

### **9.4 Secondary Endpoint Assessments (Change in below calculated between Weeks 0 and 24)**

- Abdominal SAT and VAT:SAT ratio, as calculated from single slice CT scan (as above)
- Total cholesterol, HDL cholesterol, triglycerides, LDL cholesterol (direct)
- Markers of inflammation

- Insulin, glucose, HOMA-IR
- Framingham Risk Score calculation
- Prevalence of metabolic syndrome
- Systolic and diastolic blood pressure measurements
- Urinary protein excretion and serum creatinine measurement

## 9.5 Study Monitoring

This is an open label study. Accrual and a summary of all Grade  $\geq 2$  signs and symptoms and all Grade  $\geq 3$  laboratory abnormalities will be prepared by the central data management site at UCLA, and reviewed by the team monthly. Baseline characteristics, early treatment discontinuations, and study discontinuations will be reviewed by the protocol chairs. The data management center at UCLA will also prepare a quarterly report of all AEs for review.

An independent Data Safety Monitoring Board (DSMB) comprised of three HIV investigators not involved in the study will review accrual, AE summaries, off-treatment, and off-study rates quarterly. A DSMB review may also be convened if a reason is identified by the study chairs, the data management center at UCLA, or the pharmaceutical sponsor.

## 9.6 Analyses

All statistical tests will be two-sided with nominal level of 0.05. Analysis will be exploratory without adjusting for multiple testing.

### 9.6.1 Primary Analysis

Comparison of VAT volume change between Weeks 0 and 24 will be assessed using the paired t test. The primary analysis will be as-treated, excluding subjects who do not remain on the study regimen and/or subjects who do not have an observed primary endpoint. Subjects who discontinue telmisartan for  $\geq 14$  consecutive days will not contribute to the primary outcome after the date they first discontinued medication. An intent-to-treat analysis will be performed as a supplement.

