## **1.0 STUDY HYPOTHESIS AND OBJECTIVES:**

### **1.1 Hypothesis**

In HIV-positive subjects with central fat accumulation on ART, daily telmisartan therapy will be associated with a 10% reduction in visceral adipose tissue over 24 weeks.

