### **1.2 Primary Objectives:**

1.2.1 To assess the median change in visceral adipose tissue (VAT) volume (measured by abdominal CT scan) over 24 weeks in HIV-positive subjects with central fat accumulation initiating telmisartan therapy.

1.2.2 To describe the safety and tolerability of telmisartan in HIV-positive men and women over the 24 week duration of the study.

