## **9.0 SAMPLE SIZE AND ENDPOINTS**

### **9.1 Sample Size**

In a recently reported study of growth hormone releasing factor in HIV lipodystrophy, the FDA determined an 8% change in visceral abdominal fat between the active and placebo arms would define a clinically meaningful difference in VAT volume, assuming a standard deviation of 18.5%. However, we will aim for 10% difference in visceral fat to make it more clinically significant.

Using the parameters recommended by the FDA, we estimate that a sample size of 27 subjects will provide 80% power to detect a 10% reduction in VAT over 24 weeks in subjects treated with telmisartan (two-sided alpha level=0.05). We have increased the sample size to 35 subjects to improve our power to look at secondary endpoints, and to account for potential loss of follow-up. The total sample size is 35 subjects.

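### The primary test names no scale for the VAT change, so the 80% power planned for mean percent change is not established for the test as written

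*Protocol*

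**What the plan says.** Five places in the protocol describe the primary question.

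- Section 1.1 (hypothesis) uses a percent: "daily telmisartan therapy will be associated with a 10% reduction in visceral adipose tissue over 24 weeks".
- Section 1.2, objective 1.2.1, uses a median: "To assess the median change in visceral adipose tissue (VAT) volume".
- Section 9.1 sizes the trial in percent: "we estimate that a sample size of 27 subjects will provide 80% power to detect a 10% reduction in VAT over 24 weeks". The spread comes from the growth hormone releasing factor study, where a given difference "would define a clinically meaningful difference in VAT volume, assuming a standard deviation of 18.5"%. The level is "two-sided alpha level=0.05". Enrolment is then raised to 35, partly for secondary endpoints and partly for losses.
- Section 9.3 gives VAT in cm², and says that it "will be calculated from a single 5 mm slice CT scan obtained at the level of the L4-L5 inter-vertebral disc space".
- Section 9.6.1 names the test: "Comparison of VAT volume change between Weeks 0 and 24 will be assessed using the paired t test". It does not say whether the change is absolute, percent or logarithmic. The primary set is as-treated and needs an observed endpoint.

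Section 9.6 adds that "All statistical tests will be two-sided with nominal level of 0.05" and calls the analysis exploratory.

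**The concern.** A paired t test works on the mean of the within-subject differences. Section 9.3 supplies values in cm² and section 9.6.1 mentions no transformation, so the natural reading is a test of mean cm² change. That estimates neither the 10% of the hypothesis nor the median of the objective, and the power in section 9.1 was calculated for something else.

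Two things are at stake. First, the power statement is not tied to the test. Second, with about 30 subjects in an open-label trial, an unnamed scale leaves absolute, percent or log change, and mean or median, to be chosen after the data are seen. These can give different p-values. On the cm² scale, a few subjects with very large VAT may dominate the result.

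**Working it through.** **Inputs from section 9.1.** Effect 10%, SD 18.5% (taken as the SD of individual percent change), two-sided alpha 0.05, power 80%, 27 subjects, 35 enrolled. The protocol gives no mean or CV for baseline VAT and no SD for cm² change.

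**1. The plan's own figure.** The one-sample normal approximation is n = [(z₀.₉₇₅ + z₀.₈₀) × SD/δ]² = [(1.960 + 0.842) × 18.5/10]² = 26.86, rounded up to 27. The plan's number reproduces, and it belongs to mean percent change.

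**2. The same effect with a t test.** Noncentral t with noncentrality (10/18.5) × √n gives:

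| n | Power, percent change |
|---|---|
| 27 | 77.1% |
| 28 | 78.7% |
| 29 | 80.2% |
| 35 | 87.4% |

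This is a small-sample correction of two subjects. It has nothing to do with the choice of scale.

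**3. cm² change, if percent change is independent of baseline VAT.** Scale baseline to mean 1 with CV c (assumed). The mean change is 0.10 and its SD is √[(1 + c²)(0.185² + 0.10²) − 0.10²].

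| c | SD | Power at 27 | Power at 35 | n for 80% |
|---|---|---|---|---|
| 0.2 | 0.190 | 75.1% | 85.8% | 31 |
| 0.3 | 0.195 | 72.5% | 83.7% | 32 |
| 0.4 | 0.203 | 69.2% | 80.7% | 35 |
| 0.5 | 0.213 | 65.2% | 77.1% | 38 |
| 0.6 | 0.224 | 60.8% | 72.8% | 42 |

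The noncentral t treats the cm² changes as normal. Simulation without that shortcut gives about 76% to 66% at 27 over the same range.

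**4. cm² change, if it is itself independent of baseline VAT.** Take a lognormal baseline with mean 1 and CV c (assumed), and keep percent change at mean 10% and SD 18.5%. Since E[1/B] = 1 + c² and E[1/B²] = (1 + c²)³, the mean change is 0.10/(1 + c²) and its SD is √[(0.185² + 0.10²)/(1 + c²)³ − mean²].

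| c | Mean | SD | Power at 27 | Power at 35 |
|---|---|---|---|---|
| 0.2 | 0.096 | 0.173 | 79.2% | 89.0% |
| 0.3 | 0.092 | 0.160 | 81.6% | 90.8% |
| 0.4 | 0.086 | 0.145 | 84.7% | 92.9% |
| 0.5 | 0.080 | 0.127 | 88.1% | 95.0% |

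Against 77.1% for percent change at 27, the move to cm² lowers power under step 3 and raises it under step 4. The protocol offers nothing to decide between them.

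**The case against.** The strongest reply is that section 9.6.1 does not actually say cm². Section 9.3 gives the unit of the scan reading, while sections 1.1 and 9.1 both speak in percent, and a one-sample t test on percent change would fit section 9.1 exactly. The analysis plan, not shown here, might say so. This stands in part: the cm² reading is an inference. But the protocol itself fixes a test and an objective that do not match, and a later document could settle the matter only by departing from one of these sections. The median in 1.2.1 conflicts with a t test on any scale, although that wording does not alter the power of the t test.

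A reader might go further and infer that the 80% is lost because the test is in cm². The documents do not support this. The direction of the effect on power depends on how change relates to baseline VAT, and it is not generally true that the SD of cm² change is larger relative to its mean.

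A reader might also infer that the trial is too small. On percent change, 35 evaluable subjects give 87.4%, and even under the unfavourable model they keep 80% up to a CV of about 0.4. What remains is that part of the margin is meant for losses, and the as-treated set could bring the evaluable number down towards 27. No loss rate is stated.

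**Conclusion.** The inconsistency stands: percent in the hypothesis and the sizing, a median in the objective, cm² in the endpoint, and a t test of a mean with no scale. The protocol does not establish 80% power for the test as written. Without the SD of cm² change, power at 27 could be about 61% to 75% or about 79% to 88%. Both ranges rest on assumed baseline CVs (0.2 to 0.6 and 0.2 to 0.5) and opposite assumptions about baseline dependence, so neither is a corrected figure. Separately, and needing only the protocol's own inputs, 27 is two short for a t test on percent change (77.1%, against 80.2% at 29), which enrolment of 35 covers.

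The weight is moderate. This is a single-arm pilot with a declared exploratory analysis, the cure is wording, and nothing shows that enrolment must change.

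**What to change.** - **Section 9.6.1:** define the primary variable as each subject's percent change in VAT from Week 0 to Week 24. Test it with a one-sample t test, and report the mean with a 95% CI to be compared with 10%.
- **Objective 1.2.1:** change to the mean percent change, with the median reported as a supplement.
- **Section 9.1:** state 29 evaluable subjects for 80% power (27 give 77%, 35 give 87%), so that 35 enrolled allows 35 − 29 = 6 non-evaluable subjects.

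A log ratio would also be acceptable, but section 9.1 would then need power from an SD on the log scale and must not reuse the 29 and 77% figures. For example, if percent change were normal with mean −10% and SD 18.5%, the log change would have mean about −0.128 and SD about 0.219. Power would be about 83% at 27, and the back-transformed effect would be about −12%, not −10%.

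The cost is wording in three sections, with no extra subjects or data. The stated evaluable number becomes slightly less favourable (29 instead of 27), and the room for losses falls from 8 to 6.

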### 9.6.2 Occurrence of Study-Related AEs

The number of subjects who experience treatment-related AEs between Weeks 0 and 24 will be reported.

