### Signs and Symptoms

At entry, record all signs and symptoms occurring in the 30 days prior to entry. After entry, record all signs and symptoms  $\geq$  Grade 2. This study will use the DAIDS toxicity grading system (see Manual of Operations). Any signs or symptoms that led to a change in the study drug (telmisartan), regardless of grade, must be recorded.

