## **6.6. Laboratory Evaluations**

Fasting will be required for study entry, Week 12, and Week 24. Fasting will be defined as nothing by mouth except water and medications for at least 8 hours prior to the lab draw. At screening and entry, all laboratory values must be recorded on the CRFs regardless of grade. For post-entry assessments, record all laboratory values  $\geq$  Grade 2. Any laboratory value that led to a change in study treatment (telmisartan), regardless of grade, must be recorded. Fasting lab studies include: total cholesterol, LDL cholesterol, triglycerides, HDL cholesterol, glucose, and insulin.

**Sites must refer to the Division of AIDS Table for Grading the Severity of Adult and Pediatric Adverse Events** (see Manual of Operations), **Version 1.0, December 2004, to establish grading.**

The table is available on the telmisartan study website at  
<http://www.uclacarecenter.org/MATHtrial.org>.

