### 9.6.3 Proportion of Subjects who Discontinue Study Treatment

The proportion of subjects who discontinue study treatment prior to Weeks 12 and 24 will be summarized. Reasons for discontinuing study drug (telmisartan) will be listed.

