## **10.4 Serious Adverse Event Reporting**

The serious adverse event (SAE) reporting requirements and definitions for this investigator-initiated study, and the methods for reporting of SAEs to the Regulatory Center at the University of California at Los Angeles (UCLA) are defined according to UCLA policies and regulations. Standard post-marketing reporting of SAEs will be performed to the maker of the drug, Boehringer Ingelheim. Guidelines for SAE reporting are included in the MOP and available on the UCLA MATH study website: <http://www.uclacarecenter.org/MATHtrial.html>.

The study agent for SAE reporting is telmisartan.

SAEs must be documented on the Serious Adverse Event Reporting form (available in the MOP) and on the MATH study website: <http://www.uclacarecenter.org/MATHtrial.html>.

The study chairs (Drs. [name] or [name]) must be notified of any Grade 3 or greater toxicity that does not have an etiology clearly documented as not related to telmisartan.

All Grade 4 events, death, persistent or significant disability, incapacity, hospitalization, prolongation of hospitalization, or event that the site investigator deems medically significant and related possibly, probably, or definitely to telmisartan must be reported by completing and faxing the SAE Reporting form to [contact].

Serious Adverse Events must be reported during the protocol-defined SAE Reporting period, which is from enrollment until four weeks following the subject's last dose of study drug.

After the end of the protocol-defined SAE Reporting Period (stated above), sites must report serious, unexpected, clinically-suspected adverse drug reactions if the study site staff becomes aware of the event on a passive basis, i.e., from publicly available information.

The DSMB will be notified of any serious AEs in real time, and will also receive quarterly SAE reports for review.

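### Section 9.6.2 fixes the adverse-event summary as treatment-related events only, which is narrower than primary objective 1.2.2 and hides the all-cause burden

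*Protocol*

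**What the plan says.** Protocol 1.2.2 sets as a primary objective: "To describe the safety and tolerability of telmisartan in HIV-positive men and women over the 24 week duration of the study". Nothing there restricts safety to attributed events.

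Section 9.6 then plans two analyses that bear on it directly:

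- 9.6.2: "The number of subjects who experience treatment-related AEs between Weeks 0 and 24 will be reported". The section does not say who attributes events or what degree of suspicion counts as related. Its heading speaks of study-related events, its text of treatment-related ones.
- 9.6.3: "The proportion of subjects who discontinue study treatment prior to Weeks 12 and 24 will be summarized". It adds: "Reasons for discontinuing study drug (telmisartan) will be listed". This has no attribution filter.

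Section 9.4 also lists changes in blood pressure, serum creatinine and urinary protein among the secondary endpoints.

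On design, 9.2 states: "Subjects will not require randomization as this pilot study is a single arm, open label trial".

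On data capture, Section 6.5 (Signs and Symptoms) says "After entry, record all signs and symptoms" of Grade 2 or higher, and Section 6.6 says "For post-entry assessments, record all laboratory values" of Grade 2 or higher. Both add events of any grade that changed study drug. Neither depends on attribution.

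**The concern.** The objective asks for a description of safety. The analysis section answers with a filtered count, and the filter is an opinion on causation. Where the Protocol says who forms that opinion (7.2, 7.3, 8.3, 10.4), it is generally the investigator, who knows that every subject takes telmisartan. Subjects also take antiretrovirals and may be treated for hypertension, diabetes or lipids, so another explanation is often at hand. No control arm shows what the background event rate would have been.

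Two teams seeing identical events could therefore report quite different numbers under 9.6.2, and the reader would have no all-cause figure to set beside them. This concerns how a primary objective is reported. It does not touch the visceral fat endpoint, its power or its test.

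**Working it through.** **Step 1: objective against analysis.** What each planned output covers:

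| Output | All causes? | Subjects who stay on drug? | Adverse events as such? |
|---|---|---|---|
| 9.6.2 related events | No | Yes | Yes |
| 9.6.3 discontinuation | Yes | No | Only as a listed reason |
| 9.4 blood pressure, creatinine, urinary protein | Yes | Yes | No (mean or median change) |
| 9.5 monitoring summaries | Yes | Yes | Yes, but for ongoing review, not the final analysis |

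No row of the planned analysis gives all-cause adverse events in subjects who continue. That group matters, because 7.1 lets subjects with Grade 1 or 2 events continue on drug.

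**Step 2: is the all-cause count available?** Largely yes. Sections 6.5 and 6.6 record all signs, symptoms and laboratory values of Grade 2 or higher after entry. Section 9.5 already has summaries of all Grade 2 or higher signs and symptoms and all Grade 3 or higher laboratory abnormalities prepared monthly, and a report of all adverse events quarterly. Two limits apply. Grade 1 events after entry are not routinely recorded, and the schedule (6.1, and Visit 8 in 6.2) has no visit after Week 24. Only SAEs have a later window, in 10.4: "from enrollment until four weeks following the subject's last dose of study drug".

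**Step 3: how far attribution can move the number.** The Protocol states no adverse-event figure to reproduce. The one input from it is N = 35 (9.1). The rest are assumptions: an all-cause rate p of 20% to 60%, and a share q of 25% to 75% of affected subjects having an event judged related.

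All-cause subjects = 35 × p. Subjects reported under 9.6.2 = 35 × p × q.

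| p | All-cause | q = 25% | q = 50% | q = 75% |
|---|---|---|---|---|
| 20% | 7 | 1.8 | 3.5 | 5.2 |
| 40% | 14 | 3.5 | 7.0 | 10.5 |
| 60% | 21 | 5.2 | 10.5 | 15.8 |

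Within each row the reported count varies by 75/25 = 3, with the events themselves unchanged.

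**Step 4: can the reader work backwards?** Suppose 9.6.2 reports 7 of 35 (20%, exact 95% CI 8.4% to 36.9%). Within the same assumed ranges, that is equally consistent with:

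- 10 of 35 with any event (29%, CI 14.6% to 46.3%), since 7/10 = 70% attributed;
- 14 of 35 (40%, CI 23.9% to 57.9%), since 7/14 = 50%;
- 21 of 35 (60%, CI 42.1% to 76.1%), since 7/21 = 33%.

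The interval around the related count describes sampling error only. It does not cover this spread.

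**The case against.** The strongest reply has four parts.

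*A separate analysis plan may supply the missing table.* All-cause tables are routine there, and 9.6.2 does not forbid them. This is fair, and it means the finding is not that all-cause data are absent from the trial. But 9.6.2 is not silent: it positively selects the related-only count as the adverse-event summary for a primary objective.

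*Safety is covered elsewhere.* A reader might infer that 9.6.2 is the only safety analysis. It is not. Section 9.6.3 covers discontinuation for any cause with reasons, and 9.4 follows blood pressure and renal measures, the problems for which 5.1 allows a dose change. This part stands and narrows the gap to adverse events in subjects who stay on drug.

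*The direction of error is unknown.* A reader might infer that the filter always makes the drug look safer. The related count cannot exceed the all-cause count, but attribution can err either way. Sections 7.2 and 8.3 lean toward relatedness, withholding drug unless there is a compelling reason to think it was not the cause (7.3 is similar for Grade 4 symptomatic events), and 10.4 counts even possible relation. An all-cause count in a single arm also takes in background events. One-way bias is not shown.

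*The Week 24 limit is proper.* A reader might see a conflict with the four-week tail in 10.4. There is none: 1.2.2 is itself confined to the 24 weeks, and the tail is a reporting period for SAEs.

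Unblinded attribution also comes with the design and cannot be removed. What can be corrected is reporting it alone.

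**Conclusion.** The concern holds in limited form. Section 9.6.2 fixes a measure narrower than objective 1.2.2, dependent on uncalibrated attribution, when a better measure can be had from data the Protocol already records. The size cannot be estimated from the documents. Under the assumed attribution shares of 25% to 75%, the reported count moves threefold for the same events, and a reported 7 of 35 could stand for anything from 10 to 21 subjects with an event.

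That investigators make the attribution is inferred from 7.2, 7.3, 8.3 and 10.4, since 9.6.2 does not say. The objective is descriptive and all analyses are declared exploratory (9.6), so this is a change that should be made, not a flaw that threatens the trial's main result.

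**What to change.** Rewrite 9.6.2 along these lines:

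- Report the number and percentage of subjects with any recorded adverse event, regardless of attribution, by grade with exact 95% confidence intervals, for Weeks 0 to 24. Define a recorded event as a sign, symptom or laboratory value of Grade 2 or higher, or one of any grade that led to a study-drug change.
- Report SAEs regardless of attribution, to the extent captured, through four weeks after the last dose. The qualifier is needed because the reporting sentence in 10.4 can be read as tying some or all categories to suspected relatedness.
- Show treatment-related events as a subset, defined as possibly, probably or definitely related, the scale already used in 7.2 and 10.4.

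The definition must stay within what is recorded. Asking for every event of any grade, or for non-serious events after Week 24, would need data collection that the Protocol does not have.

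Cost: one extra table and a few sentences, with no new visit, procedure or form.

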### 9.6.3 Proportion of Subjects who Discontinue Study Treatment

The proportion of subjects who discontinue study treatment prior to Weeks 12 and 24 will be summarized. Reasons for discontinuing study drug (telmisartan) will be listed.

